### Approval

All procedures performed in this study were in accordance with the ethics standards of the institutional and/or national research committee and with the 1964 Helsinki declaration and its later amendments. This study was approved by the Ethical Committee of Grigore *T. Popa* University of Medicine and Pharmacy of Iasi (no. 110/2021). The enrolled patients will receive a written informed consent approved by the Ethical Committee, that describes the nature of the trial, aims and expected advantages, as well as possible risks, and all study participants will provide signed consent prior to enrolment.

### Screening and enrolment

All study procedures (as pointed in Table 1 and Fig. 2), including screening and enrolment, will be conducted by trained personnel with backgrounds in cardiology, nephrology, internal medicine and medical science. We will recruit participants from the investigators’ clinic patient panel at [name] Clinical Hospital of Iasi and dialysis units from Iasi. Investigators will also partner with other providers from nearby hospitals and/or dialysis centres for enrolment. We will approach participants during routine clinic visits. For retention, we will leverage the electronic medical record to track hospitalizations and scheduled clinic visits during the study period. All participants will first undergo a brief screening discussion, via telephone or in person, to determine eligibility and interest. Participants will be queried on their health history including the presence of other major medical illnesses, to ensure that no exclusion criteria are present. If eligible, participants will be invited to participate in a 1-hour baseline assessment, when each participant will undertake a detailed interview in order to summarize the patient datasheet, further included into the trial database. During the baseline assessment, informed consent will be presented by the study staff including a description and timing of the study procedures, potential risks and benefits of study involvement, rights to withdraw from the study, and details regarding protections against study risks. All participants will receive a copy of their signed informed consent form.

**Table 1 Tab1:** Study procedures flowchart

Procedures/Timepoint		Study interventions			
	Enrolment	Baseline	6 months	12 months	24 months
**Enrolment**					
*Eligibility screen*	*X*				
*Contact information*	*X*				
*Informed consent*	*X*				
**Interventions**					
*FMD*		*X*	*X*	*X*	*X*
*Arterial stiffness*		*X*	*X*	*X*	*X*
*Assessment of intima media thickness*		*X*	*X*	*X*	*X*
*Echocardiography*		*X*	*X*	*X*	*X*
*LUS*		*X*	*X*	*X*	*X*
*BIS*		*X*	*X*	*X*	*X*
*Blood collection*		*X*	*X*	*X*	*X*
**Assessments**					
*Clinical data*	*X*	*X*	*X*	*X*	*X*
*IL1, IL6, VCAM-1, endoglin, NO and ADMA*		*X*	*X*	*X*	*X*
*CV risk*			*X*	*X*	*X*
*Mortality rate*					*X*
*Renal outcome*			*X*	*X*	*X*
*ED*					*X*

**Fig. 2 Fig2:**
[figure not shown]
Flow diagram of the study design

After the consent process, patients will undergo the study interventions as detailed below. At the completion of the baseline intervention, the patients will be scheduled for their second intervention session approximately 6 months later. Participants will be informed that they will continue to receive their usual medical care. After each intervention visit, the patients will receive a copy of their records, data that will be available to their physician if needed.

### Study interventions

All the proposed performed procedures are described in Table 2 with a special attention on the used protocol and the obtained result.

**Table 2 Tab2:** Protocol for the study procedures

Procedure	Protocol description
FMD	- use of Philips CX50 Ultrasound System with a 12-Mhz probe; - the vasoactive medications removal for 24 h before the procedure; - patient in supine position for at least 15 min before the examination; - the right arm will be immobilized in the extended position for the brachial artery 2–4 cm above the antecubital fossa recording; the contralateral arm will be used if an arteriovenous fistula is present; - 3 adjacent measurements of end-diastolic brachial artery diameter will be made from single 2D frames; - the cuff will be inflated up to 50 mmHg higher value of systolic blood pressure and kept this way for 5 minutes; - the maximum FMD diameters will be analysed from the average of the 3 consecutive maximum diameter measurements, and 1 minute after the cuff will be deflated; - the FMD will be calculated as the percentage change in diameter compared with baseline resting diameters, in agreement with the criteria set by the International Brachial Artery Reactivity Task Force.
Arterial stiffness	- applanation tonometry using SphygmoCorTM; PWV Inc., Westmead, Sydney, Australia; - the patient will be recumbent 10 minutes before the measures; - measurements: sequentially pulse of the carotid and femoral, the transit time from the R-wave of the simultaneously acquired electrocardiogram to the foot of the carotid and femoral pulse, and the difference acquired electrocardiogram to the foot of the carotid and femoral pulse; - the carotid-femoral PWV will be calculated from the difference between these 2 transit times divided by distances measured from the body surface (arterial path length).
IMT	- Philips CX50 Ultrasound System with a 12 MHz probe; - high-resolution B-mode ultrasound of the common carotid arteries with scanning of the longitudinal axis until the bifurcation and of the transversal axis will be performed; - two longitudinal measurements will be obtained for each carotid artery, by rotating the vessels at 180^o^ increments along their axis; - IMT will be measured at 1 cm proximal to the bifurcation on each side.
Echocardiography	- according to the American Society of Echocardiography recommendations by an observer unaware of the LUS and bioimpedance results; - measurements: cardiac anatomy (e.g. volumes, geometry, mass) and function (e.g. left ventricular function, valvular function, right ventricular function, and pulmonary artery pressure); - in patients with adequate acoustic windows, both left ventricular global longitudinal strain (LVGLS) and right ventricular free wall strain (RVFWS) will be calculated.
LUS	- patient in the supine position; - measurements of the anterior and lateral chest on both sides of the chest, from the second to the fourth (on the right side to the fifth) intercostal spaces, at parasternal to mid-axillary lines; - B-lines will be recorded in each intercostal space and were defined as a hyperechoic, coherent US bundle at narrow basis going from the transducer to the limit of the screen; − B-lines starting from the pleural line can be either localized or scattered to the whole lung and be present as isolated or multiple artifacts; - the sum of B-lines produces a score reflecting the extent of lung water accumulation (0 being no detectable B-line).
BIS	- portable whole-body multi-frequency bioimpedance analysis device (BCM®Body Composition Monitor – Fresenius Medical Care D GmbH); - electrodes will be attached to the patient’s forearm and ipsilateral ankle, with the patient in a supine position; - measurements: body resistance and reactance to electrical currents of 50 discrete frequencies, ranging between 5 and 1000 kHz; - calculations: ECW, ICW and TBW, to determine the amount of fluid overload; - AFO is defined as the difference between the expected patient’s ECW under normal physiological conditions and the actual ECW, whereas RFO is defined as the absolute fluid overload AFO to ECW ratio.
Blood collection for biomarker evaluation	- whole blood will be collected in gel & clot activator tubes (minimum 3.5 mL tube) at each intervention visit for each patient; - serum will be collected by centrifugation and frozen in aliquots at −80 ° C until further analysis; - IL1, IL6, VCAM-1, endoglin, NO and ADMA in serum samples will analysed by specific enzyme linked immunosorbent assay (ELISA) kits on a Sunrise Basic Tecan microplate reader.

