### Outcome data

***The primary outcomes of this study*** will be all-cause mortality rate, a composite CV outcome (time to first non-fatal myocardial infarction, non-fatal stroke, and hospitalization for heart failure or CV death) and long-term impact of the COVID-19 on markers of CV risk and ED in all included patients.

***Secondary outcomes*** are defined as a composite of renal outcome: doubling of creatinine or a 40% decline in eGFR or dialysis initiation in CKD or KTx patients.

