### Sample size power calculation

According to sample size power calculations, including 125 patients in each group will provide statistical power (alpha 0.05 and power 80%) for an estimated difference in the mortality rate of 9% [29] in the non-COVID group compared to 22% mortality in the COVID positive group [30–34].

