FMD is a widely recognized indicator of both subclinical atherosclerosis and coronary artery endothelial function [48], with important prognostic value [49]. Compared with healthy controls, significantly lower FMD values were reported during the acute phase of COVID-19 [50, 51]. In addition, FMD was an independent predictor of mortality in this setting [51, 52]. FMD was also assessed in the post-COVID population, with evidence suggesting the persistence of impaired FMD at 3 months distance after the acute event [53]. In a study that included 133 convalescent moderate-to-severe COVID-19 patients and 133 matched controls, FMD values were significantly lower within 2 months from COVID-19, and were directly correlated with the severity of pulmonary disease. However, this difference was nullified by female gender, smoking or the presence of more than 3 concomitant risk factors [54]. Thus, one can conclude that COVID-19 is an independent predictor of ED [55]. Interestingly, pulmonary rehabilitation increased FMD with ~ 2% among 82 patients with a history of severe or critical COVID-19 [56].

Arterial stiffness is a risk factor for in-hospital mortality in COVID-19 patients [57] and also for increased hospitalization duration [58]. PWV is also increased in patients with prior COVID-19 disease [59, 60].

The up-to-date review of Samprathi and Jayashree [61] presents the rational use of available biomarkers in the diagnosis and management of patients with COVID-19. The authors discuss based on Sars-CoV-2 pathophysiology, the laboratory tests offered to the clinician, from hematological, inflammatory, coagulative and biochemical parameters and up to cardiac biomarkers. The combined hematological biomarkers, namely increased leukocytes, neutrophils, CRP, PCT and ferritin, cytokine levels (IL-2R, IL-6, IL-8, IL-10 and TNF-α) and decreased lymphocyte counts predicts the severity of the disease and hospital admission. At inflammatory level, elevated CRP, PCT, cytokines (IL-6, IL-1b, IL-2, IL-8, IL-17, G-CSF, GMCSF, IP-10, MCP-1, CCL3, and TNFα) values forecast also, predicts progression to severe disease. Raised cardiac biomarkers involving CK, CK-MB, LDH, Mb, cTnI, α-HBDH, AST, and NT-proBNP were observed especially in severe illness and were associated with higher mortality. The proposed biomarkers play an essential role in early suspicion, diagnosis, monitoring, and recognition of acute complications, but what about on the long-term effects of COVID-19?

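### Table 2 states the carotid-femoral PWV rule upside down (time over distance), which would reverse the marker's direction if applied literally

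*Protocol article*

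**What the plan says.** The arterial stiffness row of Table 2 (Study interventions) describes tonometry at the carotid and femoral sites, with each transit time taken from the R-wave to the foot of the pulse. It then gives the computing rule: "the carotid-femoral PWV will be calculated from the difference between these 2 transit times divided by distances measured from the body surface". A closing bracket identifies those distances as the arterial path length.

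The Discussion describes arterial stiffness as a risk factor for in-hospital death in COVID-19 and adds that "PWV is also increased in patients with prior COVID-19 disease". PWV is listed in the Objectives and measured at baseline and at 6, 12 and 24 months (Table 1). Outcome data counts among the primary outcomes the "long-term impact of the COVID-19 on markers of CV risk and ED in all included patients", without listing the markers.

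The bioimpedance (BIS) row of the same table gives its purpose as "calculations: ECW, ICW and TBW, to determine the amount of fluid overload". It states that "AFO is defined as the difference between the expected patient’s ECW under normal physiological conditions and the actual ECW", and that "RFO is defined as the absolute fluid overload AFO to ECW ratio".

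**The concern.** A pulse wave velocity is a distance divided by a time. The rule in Table 2 names a time as the numerator and a distance as the denominator, and the division is explicit, so no reading of the sentence yields m/s. This is a stated formula that is wrong, not a detail left to another document.

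What is at stake is direction. Stiffer arteries conduct the pulse faster, which shortens the transit-time difference and lowers the quantity as written. Anyone applying the table literally would read a stiffer group as the less stiff one, and the signs of correlations, regression coefficients and hazard ratios involving PWV would be misread in the same way.

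The BIS row raises a smaller question. Absolute fluid overload (AFO) is a signed quantity, because actual extracellular water (ECW) can lie above or below the expected value. The row does not say which is subtracted from which. Nor does it say whether the ECW in the denominator of relative fluid overload (RFO) is the actual or the expected value.

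**Working it through.** The article gives no numerical PWV or fluid value, so there is no stated figure to reproduce. The check is one of units and direction. All numbers below are illustrative assumptions.

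**PWV: units**
- Table 2: (femoral - carotid transit time) / path length = s / m.
- Velocity: path length / (femoral - carotid transit time) = m / s.
- The first is exactly 1 / the second.

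**PWV: direction** (assumed path length 0.50 m)

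| Transit-time difference | Distance / time | Table 2 as written |
|---|---|---|
| 0.070 s (more compliant) | 0.50 / 0.070 = 7.1 m/s | 0.070 / 0.50 = 0.14 s/m |
| 0.050 s | 0.50 / 0.050 = 10 m/s | 0.050 / 0.50 = 0.10 s/m |
| 0.040 s (stiffer) | 0.50 / 0.040 = 12.5 m/s | 0.040 / 0.50 = 0.08 s/m |

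From 0.050 s to 0.040 s the velocity changes by 12.5 / 10 - 1 = +25%, and the written quantity by 0.08 / 0.10 - 1 = -20%. From 0.070 s to 0.040 s the changes are +75% (0.070 / 0.040 = 1.75) and -43% (0.08 / 0.14 = 0.57). The ranking reverses for any positive path length and transit-time difference, so the conclusion does not depend on the values chosen.

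**PWV: effect on the planned analyses** (Statistical analysis section)
- Kruskal-Wallis: a reciprocal reverses the ranks. The p-value is unchanged and the direction reverses.
- Log-converted PWV: log(1/x) = -log(x). Only the sign of the coefficient changes.
- Untransformed ANOVA, Pearson correlation, linear regression or Cox models: the reciprocal is a non-linear change of scale, so effect sizes and p-values can change as well as direction.

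**AFO and RFO: what the wording leaves open** (assumed expected ECW 15 L, actual ECW 18 L)
- Actual minus expected: 18 - 15 = +3 L; RFO = 3 / 18 = +16.7%.
- Expected minus actual: 15 - 18 = -3 L; RFO = -3 / 18 = -16.7%.
- With expected ECW as denominator, the size of RFO would be 3 / 15 = 20% instead of 16.7%.

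The row's wording does not decide between these, although its stated purpose favours a positive value for excess fluid.

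**The case against.** The strongest reply is that this is a drafting slip without consequence. The measurement comes from a named tonometry system, and nothing in the article says that staff calculate PWV by hand from Table 2. The quantity is called a velocity throughout, the Discussion reads it in the right direction, and another clause in the same row is visibly garbled. Ranks and logs lose only the sign. All-cause mortality, the cardiovascular composite and the mortality-based sample size (9% against 22%) are untouched. PWV is also not named in the primary outcome; that it belongs there is a reasonable inference from the reference to markers of cardiovascular risk.

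Most of this stands, and it limits the harm. It does not rescue the rule. Table 2 is presented as the protocol for the study procedures, and the formula in it contradicts both the name of the measure and the article's own interpretation of it.

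A reader might also infer that the fluid-overload rule is reversed, since expected ECW is named first. The text does not support that: it contains no subtraction, a difference between two quantities is ordinary wording for a gap, and the stated aim of measuring overload points to positive values for excess. Nor does it follow that the planned log conversion fails because of the order of subtraction. AFO can be negative under either order, and log conversion is planned only for non-normally distributed variables.

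**Conclusion.** The PWV rule in Table 2 is inverted, and this can be established from the text alone. Applied literally, it gives s/m and reverses the direction of the marker, against the Discussion. In the illustration a 25% rise reads as a 20% fall; the percentages rest on assumed values, but the reversal does not.

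Harm to the data is conditional. It arises only if someone computes or recomputes PWV from the table, and the documents do not show that any stored value is wrong. A reader might infer that the trial's PWV results will come out reversed; that goes further than the text allows.

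For fluid overload, the finding is only an unstated sign convention and an unspecified denominator.

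**What to change.** In Table 2, arterial stiffness row, write: PWV (m/s) = carotid-femoral path length / (femoral transit time - carotid transit time).

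Enrolment began in January 2021, and data pass through paper forms into a database, so run a range check that PWV values already entered are in m/s. Device output may already be correct, in which case nothing changes. The check should be made in metres and seconds, where the two forms are far apart (7.1 to 12.5 against 0.08 to 0.14 in the illustration). In centimetres and milliseconds both lie near 1 (50 / 40 = 1.25 cm/ms against 40 / 50 = 0.8 ms/cm) and would be hard to tell apart.

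As a clarification in the BIS row, state that AFO (L) = actual ECW - expected ECW, with positive values meaning overload, and that RFO = AFO / actual ECW. Confirm that entered values carry that sign.

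The cost is two lines of text and one database check. Design, sample size and study visits are unaffected.

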More and more studies are reporting the persistence of COVID-19 related symptoms for more than a month after the acute episode, recently defined as post-COVID syndrome*.* The percentage of incessant symptomatology varies from 35 to 89.2% [17, 18] and it is independently associated with age [17], two or more comorbidities and the severity of the acute disease [18–21]. It looks that women are more predisposed to experience remaining symptoms [22]. The laboratory abnormalities are also frequently reported. An increase in D-dimer, interleukin-6 (IL-6), C-reactive protein (CRP), fibrinogen level as well as lymphocyte count may serve as predictors for long COVID [23]. The percentage of renal transplant recipients who survived acute COVID-19 and had no clinical symptoms or were free from any laboratory abnormalities after 2 months from the initial diagnosis was 11.53%. Sustained clinical symptoms were found in 45.2%, and one or more laboratory abnormalities were reported in 71.2%. Long-term complications in these patients were strongly predicted by diabetes mellitus, hospitalization in the acute setting, renal allograft function, as well as laboratory abnormalities [24].

COVID-19 survivors have higher risks of AKI, de novo development or worsening of proteinuria, eGFR decline and progression to ESKD. These outcomes are reported even among patients those with mild symptoms and increase with the severity of the infection [25].

The underlying mechanisms of these manifestations and long-term complications are not completely understood, but emerging data emphasize the endothelium, as a central pillar in the long COVID conundrum, with implications in inflammation, the pro-thrombotic phenotype and disseminated intravascular coagulation [26]. Endothelial dysfunction (ED) refers to a systemic condition in which the endothelium loses its physiological properties, including the tendency to promote vasodilation, fibrinolysis, and anti-aggregation [13]. Morphologic findings from deceased patients confirm the presence of viral elements within endothelial cells and an accumulation of inflammatory cells, with evidence of endothelial and inflammatory cell death. Endotheliitis in several organs as a direct consequence of viral involvement and of the host inflammatory response may explain the impaired microcirculatory function in different vascular beds and clinical sequelae in patients with COVID-19 [27].

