#### Inclusion criteria

Age > 18 years;Patients with CKD stage 3–5, including dialysis or KTx with confirmed COVID-19, at minimum 2 weeks after the confirmed test;Age, sex and kidney disease (CKD stage 3–5, dialysis or KTx) matched patients without confirmed SARS-CoV-2 infection.

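### Table 2 plans to measure nitric oxide by ELISA in stored clotted serum, which cannot be done as written; the analyte and method need to be named, with renal function built into the comparison

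*Protocol article*

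**What the plan says.** The blood-collection row of Table 2 (Study interventions) fixes the whole handling chain. On collection: "whole blood will be collected in gel & clot activator tubes (minimum 3.5 mL tube) at each intervention visit for each patient". On storage: "serum will be collected by centrifugation and frozen in aliquots at" −80 °C. On assay: "IL1, IL6, VCAM-1, endoglin, NO and ADMA in serum samples will analysed by specific enzyme linked immunosorbent assay (ELISA) kits". The Abbreviations list expands NO as nitric oxide. The document mentions neither nitrite, nitrate nor NOx, so NO is not presented as shorthand for a surrogate.

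Table 1 schedules the panel "IL1, IL6, VCAM-1, endoglin, NO and ADMA" at baseline and at 6, 12 and 24 months. Outcome data lists among the primary outcomes the "long-term impact of the COVID-19 on markers of CV risk and ED in all included patients", without naming individual markers.

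Four other places bear on how a nitric-oxide surrogate would behave:
- **Inclusion criteria:** the exposed group is "Patients with CKD stage 3–5, including dialysis or KTx with confirmed COVID-19", and the controls are "Age, sex and kidney disease (CKD stage 3–5, dialysis or KTx) matched patients without confirmed SARS-CoV-2 infection". Kidney disease is matched by category; no eGFR value is matched.
- **Background:** "COVID-19 survivors have higher risks of AKI, de novo development or worsening of proteinuria, eGFR decline and progression to ESKD".
- **Clinical data:** renal function is recorded, and Table 1 has clinical data collected at every visit.
- **Statistical analysis:** the between-group tests are unadjusted, and the regressions admit a covariate only if its univariate p-value is below 0.05.

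**The concern.** Five of the six analytes are plausible targets for an immunoassay in stored serum; nitric oxide is not. It is oxidised in blood within seconds, so essentially none survives clotting, and a molecule of two atoms gives an antibody nothing to bind. This is a fault in what the plan states rather than a detail left to a fuller document, because Table 2 names the analyte, the sample and the assay.

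Two results are possible if the plan is followed. A true antibody kit would return non-specific signal. A kit that in fact reads nitrite and nitrate would return a surrogate that reflects NO production but also diet and renal clearance. Neither is what the label says.

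The second case matters for the group comparison. Clearance varies widely across this population, category matching leaves room for eGFR to differ within the CKD 3–5 and transplant classes, and the document itself links COVID-19 to later eGFR decline. Matching at entry cannot correct a divergence that develops during follow-up. The correlations and stepwise regressions that use the marker would inherit the problem.

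**Working it through.** The plan gives no figure for this assay, so there is nothing to reproduce. The arithmetic below shows whether the conclusion is sensitive to its assumptions.

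**1. Does any nitric oxide remain?**
Assumptions, not in the document: half-life in blood of at most 60 s, and 30 min (1,800 s) of clotting.
Fraction left = 2^(−t/half-life) = 2^(−1800/60) = 2^(−30) ≈ 9 × 10⁻¹⁰.
A shorter half-life leaves less, so the conclusion does not depend on the exact value.

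**2. If the kit reads NOx, how much can clearance move one patient's value?**
Steady-state NOx is proportional to production/clearance. Let f be the renal share of NOx elimination; the document gives no value, so 30%, 60% and 100% are assumed. The 40% eGFR decline is a component of the study's own renal outcome. With production unchanged, the ratio is 1/(1 − 0.4f):

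| f | Ratio | Rise in NOx |
|---|---|---|
| 0.3 | 1/0.88 = 1.14 | 14% |
| 0.6 | 1/0.76 = 1.32 | 32% |
| 1.0 | 1/0.60 = 1.67 | 67% |

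These are changes within one patient who reaches that decline. They are not differences between the groups.

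**3. Can the group difference reverse?**
COVID/control ratio = (1 − production loss)/(1 − f × clearance loss), with all inputs assumed:

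| f | Production loss | Clearance loss | Ratio | Reading |
|---|---|---|---|---|
| 1.0 | 10% | 20% | 0.90/0.80 ≈ 1.12 | reversed |
| 1.0 | 20% | 10% | 0.80/0.90 = 0.89 | correct direction |
| 0.5 | 10% | 20% | 0.90/0.90 = 1.00 | difference hidden |
| 0.5 | 10% | 40% | 0.90/0.80 ≈ 1.12 | reversed |
| any | 10% | 0% | 0.90 | no bias |

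The ratio exceeds 1 only when f × clearance loss exceeds the production loss.

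**4. What might that mean at group level?**
For illustration, assume 10 percentage points more patients with a 40% decline in the COVID group and f = 0.6. The group mean shifts by about 0.10 × 32% ≈ 3%. The excess share of decliners is not in the document, so this is not an estimate for this study. The eGFR model in steps 2 to 4 does not describe dialysis patients at all.

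**The case against.** A reader might infer that whatever the assay returns must be the renally cleared end-products, so that the NO marker will track renal function and show the COVID group as having better endothelial function. The document does not support that, for four reasons.
- **Unknown signal.** The kit is not identified. If it is a true ELISA, the signal is not NOx and the renal argument does not apply. If it is a NOx microplate assay loosely called ELISA, the fault is mainly in the label and method description.
- **Unknown direction.** No section says how the NO value will be interpreted. The Background gives a higher risk of eGFR decline, not a rate for this cohort.
- **Existing protection.** Controls are matched on kidney-disease category and renal function is recorded. A strong link between the marker and renal function would probably bring renal function through the univariate screen.
- **Limited reach.** Outcome data does not name NO. It is one of six serum markers beside FMD, PWV and IMT, and the sample size rests on mortality.

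All four points stand, and they limit the consequence. They do not remove the error: analyte, sample and assay are stated together and are incompatible. The protection is also partial. The group tests are unadjusted, and passing a univariate screen makes renal function only a candidate for a stepwise model.

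**Conclusion.** The point holds as a specification error in one of six serum biomarkers: nitric oxide cannot be measured by ELISA in clotted, frozen serum. This rests on general chemistry and is insensitive to the assumed half-life.

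Confounding by renal function is a conditional second step. It applies if the kit reads nitrite and nitrate, and if elimination is partly renal. Under those conditions the group difference can be hidden or reversed, but only when renal share times clearance loss exceeds the production loss. The document supplies none of those quantities, so no size can be put on the between-group bias. The 14%, 32% and 67% figures are patient-level illustrations on assumed renal shares. The inference that the marker will run in the wrong direction, or that the endothelial outcome as a whole is compromised, goes beyond the document.

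**What to change.** 1. **Table 2:** take NO out of the ELISA list and add total nitrite plus nitrate (NOx) by a colorimetric nitrate-reductase/Griess microplate assay, on the same stored serum.
2. **Table 1 and all reports:** replace the label NO with NOx. Table 1 needs only the label changed, since it names no assay.
3. **Statistical analysis:** compare groups on NOx within kidney-disease class (CKD 3–5, dialysis, transplant). For non-dialysis patients, force eGFR from the same visit into the NOx model rather than leaving it to the univariate p < 0.05 screen.

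The cost is a different kit plus a few lines of wording. The samples are already planned, a microplate reader is already in use, and renal function is already recorded. The downside is that NOx is a weaker and less direct endothelial marker than the NO label implies, so one advertised marker is downgraded. Nothing else in the design changes.
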